### Statistical power

Simulations were conducted to estimate power and sample size for this study. In all simulations, providers were randomly assigned to the three different treatment groups with equal probability. Since all providers in the system were enrolled into an arm, there were no possible strategies to increase participation enrollment beyond running the trial for a longer period of time, as all new providers during the study period were enrolled into an arm. The following assumptions were made about the data generating process: (1) the average number of transfusion orders across UCH was approximately 30 per day at baseline, (2) opportunities to order a blood transfusion occurred at different rates for different providers, (3) providers encountered opportunities to order blood at rates of 1 time per day on average for hospitalists and 3 times per day on average for intensivists. In approximately 15% of these opportunities, the patient’s hemoglobin level was less than 7.0 g/dL. At baseline, a provider’s probability of ordering a transfusion was 1 when hemoglobin was less than 7.0 g/dL, 0.2 when hemoglobin was between 7.0 and 8.0, and 0.05 when hemoglobin was greater than 8.0.

We began the simulation with the following assumptions about the data generating process, based on the historical data or on subject matter expert input: (1) there should be on average 30–35 transfusions per day; (2) the number of active providers should be 228, evenly randomized into 3 groups (the total number of providers is not stochastic); (3) there are two different types of providers (high and low frequency): 30% of providers are high-frequency, while 70% of providers are low frequency (this is sampled stochastically in each simulation iteration). High-frequency ordering providers have a daily number of encounters following a Poisson distribution with lambda = 3 (Average of 3 per day). Low-frequency providers have a daily number of encounters following a Poisson distribution with lambda = 1 (average of 1 per day).

Patient hemoglobin (HGB) values were next simulated for all encounters, assuming HGB is normally distributed with mean = 8.3 and SD = 1, truncated at 0. We next simulated transfusion ordering for each encounter, conditional on the HGB value. The assumed probabilities for transfusion ordering for all groups under the null hypothesis (no difference between arms) is 1 for HGB < 7, 0.2 for 7 <  = HGB < 8, and 0.08 for HGB >  = 8.

We first simulated provider encounters where the provider has the opportunity to order a transfusion. In the observed trial data, we observed transfusions—thus, encounters that do not lead to a transfusion will not be observed. We generated encounters for these providers for time *t* (where *t* is the length of time the trial runs). Then, for each patient encounter, we simulated the HGB value associated with that encounter. We next simulated whether or not an encounter resulted in a transfusion order, which is conditional on HGB value and based on SME feedback. Transfusions are considered potentially guideline discordant if HGB is >  = 7 (any number of units). To explore potential effect sizes of the intervention for the primary hypothesis that groups 2 and 3 have an identical reduction in potentially guideline discordant ordering compared to group 1 (10% reduction, 15% reduction, and 20% reduction), we then decreased the assumed probabilities for transfusion ordering for encounters with HGB >  = 7 by *e*, where *e* is in (0.9,0.85,0.8). Finally, we implemented a logistic regression where each observation is a transfusion order, the outcome is guideline compliance as described above, and a fixed effect for treatment group with 2 levels (group 1 versus groups 2 + 3 combined). We tested the significance of the two-level fixed effect treatment group term against a significance level of 0.05. We replicated this simulation for each potential effect size (10% reduction, 15% reduction, and 20% reduction). To explore the difference in estimated power under each effect size for varying lengths of trial time *t,* we conducted the simulation 2000 times for each potential trial time length *t*, where *t* was 10 weeks up to 50 weeks.

For the primary objective comparison, we assumed that groups 2 and 3 (non-interruptive or interruptive alerts) had an equal probability of guideline-concordant transfusion ordering. Within this scenario, we examined three different effect sizes (the difference in the probability of guideline-concordant transfusion ordering). The first effect size (smallest) assumed a 10% reduction in the probability of a potentially guideline discordant transfusion order occurring. The second effect size assumed a 15% reduction in the probability of a potentially guideline discordant transfusion order occurring. The third effect size (largest) assumed a 20% reduction in the probability of a potentially guideline discordant transfusion order occurring. We conducted a simulation with 2000 replicates for each effect size to estimate the length of time required for the study to achieve 80% power.

Results from these simulations indicate that we will have 80% power to detect an effect size of 15% at 35 weeks and an effect size of 20% at 19 weeks. At 52 weeks, the power to detect an effect size of 10% is 64%. Since there was uncertainty in the expected effect size (no preliminary data available) and the smallest effect size explored would require longer than 52 weeks to achieve 80% power, the trial was designed a-priori to run for 52 weeks.

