#### Description of outcome (guideline-concordant pRBC transfusion)

The binary outcome of interest, guideline concordance of pRBC ordering, is defined based on the patient’s most recent pre-order hemoglobin value and the number of units ordered. An order is guideline concordant if the pre-order hemoglobin value is less than 7.0 g/dL and one unit is ordered or if the pre-order hemoglobin value is less than 6.0 g/dL and two units are ordered. Because there are other indications for pRBC ordering beyond a pre-order hemoglobin value, any order not meeting guideline concordance as described was labeled as potentially guideline discordant. We planned to collect outcome data for 18 months following the start date of the study.

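### The power simulation's stated inputs give about 74 orders per day, not 30–35; on a 7-day week neither volume yields the stated power, and the simulated outcome ignores units

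*Protocol article*

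**What the plan says.** All of the following is in the protocol article, section Statistical power, unless noted.

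- **Volume.** A first list of assumptions says "the average number of transfusion orders across UCH was approximately 30 per day at baseline". The list used for the simulation says "there should be on average 30–35 transfusions per day".
- **Providers and encounters.** "the number of active providers should be 228, evenly randomized into 3 groups"; 30% are high-frequency (Poisson mean 3 encounters per day) and 70% low-frequency (Poisson mean 1).
- **Hemoglobin.** The first list puts about 15% of ordering opportunities below 7.0 g/dL. The simulation draws values "assuming HGB is normally distributed with mean = 8.3 and SD = 1, truncated at 0".
- **Ordering probabilities.** Both lists use 1 below 7.0 g/dL. The first list continues "0.2 when hemoglobin was between 7.0 and 8.0, and 0.05 when hemoglobin was greater than 8.0"; the simulation list uses 0.2 from 7 to 8 and 0.08 from 8 upwards.
- **Simulated outcome and test.** "Transfusions are considered potentially guideline discordant if HGB is" 7 or more, whatever the number of units. The test is a logistic regression of arm 1 against arms 2 and 3 combined at the 0.05 level, for trial lengths of 10 to 50 weeks.
- **Stated power.** 80% for a 15% reduction at 35 weeks, 80% for a 20% reduction at 19 weeks, and "At 52 weeks, the power to detect an effect size of 10% is 64"%. The 52-week duration is justified from these figures.
- **Trial outcome** (Description of outcome). An order is concordant below 7.0 g/dL with one unit, or "if the pre-order hemoglobin value is less than 6.0 g/dL and two units are ordered". Every other order is potentially discordant.

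**The concern.** The article states every input to the simulation, so a reader should be able to recover both the daily order volume and the power. Neither comes out. The encounter model yields more than twice the volume that the same list requires, and two inputs appear with conflicting values. The simulated endpoint is also not the trial's endpoint: a two-unit order at 6.0–6.9 g/dL, or an order of more than two units below 6.0 g/dL, counts as concordant in the simulation and as potentially discordant in the trial.

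At stake is the justification of the 52-week duration, and what a reader can say about the effects this trial was able to detect. The second matters because the Trial status section reports stopping at 52 weeks with no difference seen between the arms.

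**Working it through.** **1. Order volume from the stated inputs**

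- Encounters per day: 228 × (0.3 × 3 + 0.7 × 1) = 228 × 1.6 = 364.8.
- Normal(8.3, 1): P(<7) = 0.0968, P(7 to 8) = 0.2853, P(≥8) = 0.6179. Truncation at 0 has no effect.
- Orders per encounter: 0.0968 × 1 + 0.2853 × 0.2 + 0.6179 × 0.08 = 0.0968 + 0.0571 + 0.0494 = 0.2033.
- Orders per day: 364.8 × 0.2033 = 74.2, which is 2.1 to 2.5 times the stated 30–35.

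Orders below 7 g/dL alone come to 364.8 × 0.0968 = 35.3 per day, which uses up the whole range before any discordant order. The alternative values do not help. With 0.05 in place of 0.08 the total is 67.4 per day. With 15% below 7.0 g/dL, those orders alone are 0.15 × 364.8 = 54.7 per day, and the total is about 84–94.

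**2. Power under the described test**

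Assumptions: 7-day week, two-sided 0.05 (the section does not give sidedness), one third of providers in arm 1. Let V be orders per day under the null, w the number of weeks and e the multiplier on ordering at 7 g/dL or above.

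- Discordant share of orders, arm 1: p1 = (0.0571 + 0.0494) / 0.2033 = 0.524.
- Arms 2 and 3: orders per encounter 0.0968 + 0.1065e; discordant share p2 = 0.1065e / (0.0968 + 0.1065e). The log odds ratio is −ln(e).
- Orders: n1 = V × 7 × w / 3; n2 = 2 × n1 × (0.0968 + 0.1065e) / 0.2033.
- Power ≈ Φ(−ln(e)/SE − 1.96), with SE² = 1/[n1·p1(1 − p1)] + 1/[n2·p2(1 − p2)].

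Worked case, 15% at 35 weeks and 30 per day: p2 = 0.483, n1 = 2450, n2 = 4515, SE = 0.0502, z = 0.1625/0.0502 = 3.24, power = Φ(1.28) = 90%.

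| Orders per day | 15%, 35 weeks | 20%, 19 weeks | 10%, 52 weeks |
|---|---|---|---|
| Stated in the article | 80% | 80% | 64% |
| 30 | 89.9% | 90.2% | 72.9% |
| 35 | 93.8% | 94.0% | 79.3% |
| 74.2 | 99.9% | 99.9% | 98.1% |

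A Monte Carlo run of the described simulation (4000 replicates) agrees: 90.2/89.8/72.7% at 30 per day, 93.9/94.7/78.6% at 35, and 99.8/99.9/98.0% with the inputs as stated. With the article's 2000 replicates the standard error is about one point (√(0.8 × 0.2/2000) = 0.9 points), so simulation noise does not explain the gaps.

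**3. Effect of leaving out units**

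The documents do not say how many orders below 7 g/dL fail on units. Let u be that share, assumed equal in all arms and untouched by the alerts. The discordant shares become p + u(1 − p). For u = 0.10 and a 15% effect they are 0.571 and 0.535, and the log odds ratio falls from 0.163 to 0.148. Power for 15% at 35 weeks:

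| Orders per day | u = 0 | u = 10% | u = 20% | u = 30% |
|---|---|---|---|---|
| 30 | 90% | 83% | 75% | 66% |
| 35 | 94% | 89% | 81% | 73% |
| 74.2 | 99.9% | 99.6% | 98.6% | 96.2% |

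**The case against.** **The error is in the cautious direction.** This stands for the volume and test as described: both stated volumes give more power than claimed, so the inputs do not show 52 weeks to be too short for a 15% or 20% effect. Even with units counted, a 15% effect at 52 weeks and 30 orders per day keeps about 95/90/82% power for u = 10/20/30%.

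**The mismatch in power depends on a 7-day week.** This also stands. The section does not state days per week. On a 5-day week, 33 orders per day gives about 82/82/62.5%, close to the stated figures. A contrast of arm 1 with only one alert arm gives about 80/80/60% at 30 per day, but that contradicts the comparison the section describes. A reader might infer that the authors used a third volume of about 22–25 orders per day, the level that a 7-day week would need; no such figure is in the article. None of these readings changes the 74 against 30–35, which is a per-day figure.

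**Ignoring units is a disclosed simplification.** It is disclosed, and all arms default to one unit, which may keep u small. The outcome section nevertheless counts units, so the stated power is for a different endpoint.

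**Consequences for conduct.** A reader might infer that the wrong volume drove the 6-month extension or the later statement that the sample size was adequate. Trial status does not say what expectation or target was used, and about 30 per day was available as a benchmark that does not depend on the encounter model. The gap between 50 simulated weeks and a 52-week figure is minor.

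**Conclusion.** The concern holds as an error in the reported power calculation. The 74 against 30–35 orders per day is plain arithmetic on one section, as are the conflicts of 0.05 with 0.08 and of 15% with 9.7%; these need no assumption. That the stated 80/80/64% follows from neither volume holds for a 7-day week and a two-sided test, and under those conditions the stated power is too low: 90–94/90–94/73–79% at 30–35 per day and about 99.9/99.9/98% at 74.

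Counting units, as the trial outcome does, lowers power by an amount the documents do not allow to be fixed.

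It would be tempting to conclude that the trial was overpowered. The documents do not support that. The simulation varies encounter rates between providers but not their ordering probability, whereas the Treatment comparisons section plans a mixed model with a provider random intercept; and the unit effect works the other way. Nor do they show that the trial was underpowered. What they show is that the power figures cannot be relied on as stated.

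**What to change.** Reconcile the two lists to one input set that reproduces the observed baseline order volume and the observed share of orders below 7.0 g/dL. State the number of ordering days per week. Simulate the actual primary outcome, including number of units, with the share of low-hemoglobin orders failing on units taken from the baseline data. Run the simulation through 52 weeks and replace the stated power figures with the results.

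The cost is a re-run of existing simulation code and a correction of the text. The trial is closed, and nothing in its conduct, outcome definition or planned test has to change.

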**Methods:**

All inpatient providers at University of Colorado Hospital (UCH) who order blood transfusions were randomized in a 1:1:1 fashion to the three arms of the study: (1) general order set improvements, (2) general order set improvements plus non-interruptive in-line help text alert, and (3) general order set improvements plus interruptive alert. Transfusing providers received the same randomized order set changes for 18 months. The primary outcome of this study is the guideline-concordant rate of pRBC transfusions. The primary objective of this study is to compare the group using the new interface (arm 1) versus the two groups using the new interface with interruptive or non-interruptive alerts (arms 2 and 3, combined). The secondary objectives compare guideline-concordant transfusion rates between arm 2 and arm 3 as well as comparing all of arms of the study in aggregate to historical controls. This trial concluded after 12 months on April 5, 2022.

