#### Treatment comparisons

The a priori primary objective comparison is between the group using the new interface (arm 1) and the two groups using the new interface with non-interruptive or interruptive alerts combined (arms 2 and 3, respectively).

If the a priori primary objective comparison is statistically significant, we will further test the secondary comparison for differences in compliance between the different alert groups, arm 2 versus arm 3.

We will conduct an exploratory comparison of the historical pre-trial data to the post trial onset data. If the primary objective comparison is statistically significant, we will compare the pre-trial data to arm 1 and then 2 and 3 combined. If the primary objective comparison is not statistically significant (no difference across arms), we will compare the pre-trial data to arms 1, 2, and 3 combined.

Hypothesis testing for both primary and secondary comparisons of the trial data will be implemented using generalized linear mixed models with the binary outcome of guideline-concordant order, group comparison(s) as a fixed effect, and a random intercept for provider. Significance testing will be set at *p* < 0.05.

The comparison of historical pre-trial data versus the post-trial onset data will be implemented using generalized linear mixed models with the binary outcome of guideline-concordant order (yes/no). We will implement an interrupted time series analysis by parameterizing this model with fixed effects including an intercept, a term for post-trial onset (intercept shift), a linear time trend, and an interaction between post-trial onset and linear time trend (slope difference). Pre-trial data is available for two years prior to the trial onset. The COVID pandemic likely affected the outcome of interest. If there are notable effects on the pre-trial (but post COVID onset) trend in guideline-concordant ordering, we will exclude the immediate period post-COVID from the historical pre-trial trend estimation.

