Our study has several strengths, including this is a pragmatic, prospective, randomized control trial at a busy academic medical center. All non-procedural inpatient areas are included, covering many subspecialty services, allowing these interventions to be generalizable at other hospitals with an EHR. All guideline concordant exceptions to the transfusion threshold of a hemoglobin of less than 7.0 g/dL causes of anemia are included, and the general improvement changes (arm 1) are applied across arm 2 and arm 3 to capture multiple indications for blood transfusions, which can help target future areas for improvements in blood utilization for specific indications in the future. The pragmatic nature of this trial with randomization allows for generalizability across other institutions that use similar EHRs.

Potential limitations of this study include that this is a single-center trial; however, our institution has robust and rising clinical volumes with a diversity of patients and providers including transplant programs that utilize large volumes of pRBC. Because this study is conducted at a large academic medical center, the frequency of which providers order blood is highly variable; the amount of blood ordered is not consistent among providers, including across trainees, attending physicians, nurses, and advanced practice providers. In addition, despite established guidelines being generally accepted, not all medical specialties have specific transfusion guidelines. To mitigate this, the statistical plan includes a hierarchical model realizing provider level variation, and we blocked the randomization by frequency based on baseline data. Lastly, we can only capture if a provider places an order to transfuse, but not when a provider correctly concludes that they do not need a transfusion and thus do not place an order for transfusion. This limitation is accounted for in the methods and statistical analysis.

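### The printed power figures come from a simulation with no between-provider variation in concordance, so they make no allowance for clustering although providers are the randomised units

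*Protocol article*

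**What the plan says.** The abstract's Methods paragraph says that inpatient providers "who order blood transfusions were randomized in a 1:1:1 fashion to the three arms of the study". Trial design and randomization adds that a provider stays in the assigned arm for every later order. Treatment comparisons sets the primary test: a generalized linear mixed model for the binary concordance of each order, with "group comparison(s) as a fixed effect, and a random intercept for provider". The Discussion gives the reason: "the statistical plan includes a hierarchical model realizing provider level variation".

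Statistical power describes a different model. It assumes that "the number of active providers should be 228", 30% of them with three encounters a day on average and 70% with one. Ordering probability is set by hemoglobin band, and at 7 or above it is multiplied by 0.9, 0.85 or 0.8 in arms 2 and 3. For the test, "we implemented a logistic regression where each observation is a transfusion order"; the only term listed is the two-level arm effect. The result is that "we will have 80% power to detect an effect size of 15% at 35 weeks and an effect size of 20% at 19 weeks", with 64% for a 10% effect at 52 weeks.

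**The concern.** Orders from one provider share that provider's habits. If providers differ in how readily they transfuse above the threshold, the effective sample size for an arm comparison is smaller than the count of orders. The primary model and the Discussion both expect such differences. The simulation leaves them out of the generated data and out of the test, so its orders are independent within provider.

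The article uses these figures to settle the 52-week duration. Trial status then says that the sample size proved sufficient and that the 12-month look pointed strongly to no difference. Results are to be published separately. A reader who measures a null result against 80%, 80% and 64% would take it as more conclusive than the simulation can show.

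**Working it through.** **Inputs from Statistical power.** 228 providers (76 in arm 1, 152 in arms 2 and 3); encounter rates 3 and 1 a day, split 30/70; hemoglobin Normal(8.3, 1); ordering probabilities 1 / 0.2 / 0.08 for below 7, 7 to 8, and 8 or more; 30–35 orders a day; a test "against a significance level of 0.05", taken as two-sided. Assumed, because the article gives no value: the SD σ of a normal provider effect on the log-odds of a discordant order, with ICC = σ²/(σ² + π²/3).

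**Step 1: the article's own figures, under independence.** The hemoglobin bands have probabilities 0.0968, 0.2853 and 0.6179. Per encounter, concordant orders are 0.0968 and discordant orders 0.2 × 0.2853 + 0.08 × 0.6179 = 0.1065, total 0.2033. Encounters are 228 × (0.3 × 3 + 0.7 × 1) = 364.8 a day, so orders are 364.8 × 0.2033 = 74.2 a day, against the stated 30–35. Independent-order power (15% at 35 weeks / 20% at 19 weeks / 10% at 52 weeks):

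| Order volume | Power |
|---|---|
| Stated in the article | 80 / 80 / 64% |
| 74.2 a day (literal inputs) | 99.9 / 99.9 / 98.1% |
| 30–35 a day, 7-day weeks | 90–94 / 90–94 / 73–79% |
| 30–35 a day, 5-day weeks | 78–84 / 79–85 / 58–65% |
| 23.35 a day, 7-day weeks (best single fit) | 81 / 82 / 62% |

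The best-fitting rate equals 23.35 × 7/5 = 32.7 per working day. The article does not say that weeks have five days, so 23.35 is a back-solved rate.

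**Step 2: add provider variance.** Multiplying ordering at 7 or above by e makes the odds ratio of a discordant order equal to e. A provider with expected x concordant and y discordant orders gets weight 1/(σ² + 1/x + 1/y). With W the sum of weights on each side,

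SE = √(1/W₁ + 1/W₂₃), power = Φ(|ln e|/SE − 1.96).

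**Worked case: 15% effect, 35 weeks (245 days), 23.35 orders a day.** The scale factor is 23.35/74.16 = 0.315. A low-frequency arm 1 provider has x = 245 × 0.315 × 0.0968 = 7.5 and y = 8.2; a high-frequency one has 22.4 and 24.6. In arms 2 and 3, y falls to 7.0 and 20.9.
- σ = 0: W₁ = 53.2 × 3.912 + 22.8 × 11.735 = 475.6; W₂₃ = 106.4 × 3.608 + 45.6 × 10.825 = 877.6; SE = 0.0569; 0.1625/0.0569 = 2.85; power 81%.
- σ = 0.3: W₁ = 53.2 × 2.893 + 22.8 × 5.707 = 284.0; W₂₃ = 106.4 × 2.724 + 45.6 × 5.483 = 539.8; SE = 0.0733; 0.1625/0.0733 = 2.22; power 60%.

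**Step 3: assumed range, 228 providers, same scenario order.**

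| σ | ICC | about 23 orders a day | 30 orders a day |
|---|---|---|---|
| 0 | 0 | 81 / 82 / 62% | 90 / 90 / 73% |
| 0.2 | 0.012 | 71 / 76 / 47% | 78 / 84 / 54% |
| 0.3 | 0.027 | 60 / 69 / 37% | 67 / 77 / 41% |
| 0.45 | 0.058 | 45 / 58 / 26% | 49 / 64 / 27% |

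Simulation with provider-clustered standard errors at 30 orders a day gave 79/81/51%, 64/77/38% and 42/61/25% for the last three rows. The formula is therefore close, and if anything slightly generous at the larger variances.

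**Step 4: why more weeks help less than the article implies.** With 228 providers, SE cannot fall below σ√(1/76 + 1/152) = 0.1405σ. At σ = 0.3 that is 0.0421. For a 10% effect, 0.1054/0.0421 = 2.50, so power cannot pass Φ(0.54) = 71% at any duration.

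**Step 5: number of providers.** At 23.35 a day, 35 weeks yield 23.35 × 245 = 5,721 orders: about 25 per provider over 228, about 3.5 over all 1640 randomised. Smaller clusters lose less.

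**The case against.** Several points on the other side stand.

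- No ICC or provider variance is given. A reader might infer that true power is below the printed figures by a known amount; the article does not support that. At σ = 0.2 the literal inputs (74.2 a day) give 96/99/76%, above all three printed figures. At 32.5 orders a day the result is 81/86/56%, so two of three are still met.
- Orders spread over many of the 1640 randomised providers would lose less than the 228-provider figures show. The article does, however, base its power on 228.
- Ordinary logistic regression is valid for data generated without provider effects. Its use is not a second defect; changing only the test would barely move the figures. Once provider variance is in the data it would not do: its simulated type I error at 52 weeks and 30 orders a day is 13%, 21% and 40% at ICC 0.012, 0.027 and 0.058.
- A reader might infer that the primary analysis is itself wrong. It is not: the planned mixed model carries the provider intercept, so the estimate, interval and test do not inherit the omission.
- The 52 weeks was not presented as the time to 80% power for every effect; the article concedes 64% for the 10% effect. All providers were enrolled, so only duration could change, and the trial is closed.

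Blocking by quartile of baseline ordering rate does not answer the point. It balances volume and leaves variation in concordance between providers.

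**Conclusion.** The concern holds in a limited form. The printed 80%, 80% and 64% apply to an ICC of zero, which conflicts with the trial's own primary model and with the Discussion. At any given order volume, adding provider variance lowers power and lengthens the time needed. With 228 providers and about 23 orders a day, an ICC of 0.027 takes 81/82/62% down to 60/69/37%.

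These sizes rest on an assumed σ, a two-sided test, the 228-provider structure and, for the lower volume, a back-solved order rate. They illustrate sensitivity and do not demonstrate a shortfall. What is affected is the justification of the sample size and the weight put on a null result; the validity of the planned test is not.

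**What to change.** Re-run the power simulation with a provider random effect in the data generation. Estimate its variance, the number of ordering providers and the distribution of orders per provider from the two years of pre-trial orders. Use the planned mixed model as the test. Reconcile the encounter inputs with the 30–35 orders a day, and state the days per week. Replace the 35-week, 19-week and 64% statements with results over a range of provider variance.

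Do not rest the claim of a sufficient sample, or the strength of a null result, on the present figures. Interpret a null result from the mixed-model confidence interval for the arm effect.

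The cost is a few days of simulation on data already held, with no extra providers or orders. The stated power will probably be less favourable.
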